**Revised definitions of cases and controls**

In keeping with the above protocol, the revised definitions for cases and controls are outlined as follows. All women are required to have a minimum of 12 months up-to-standard data in the CPRD prior to index date (date of diagnosis for the case) to be eligible for study inclusion.

Case definition

Cases are defined as all female participants of the CPRD with incident diagnosis of invasive or in situ breast cancer documented between 1^st^ January 1995 and 2017 (to most recent data available), and aged 20- 79 years of age at index diagnosis. Women are excluded if they have a past history of invasive or in situ breast cancer.

The list of Read codes used to flag women with incident breast cancer diagnosis as per previous protocol is shown Appendix 1.

Control definition

Controls are defined as all women without a medical diagnosis of breast cancer documented (up to last date of data extraction for 2017). This includes any diagnoses for breast cancer prior to 1^st^ Jan 1995 and during the study period from 1^st^ Jan 1995 to 2017. Cases are therefore not eligible to act as controls in this study.

Controls will be matched in a 2:1 ratio to cases based on:

- Year of birth(+/- 2 years)
- Same general practice
- Similar period of observation as the case.

The period of observation in CPRD for controls must include the full observation time (regstart to index diagnosis) for cases, so that observation periods may be matched exactly for the purpose of analyses.

**Appendix 1: List of read codes for identifying breast cancer diagnosis in CPRD**

| **Med Code** | **Read Code** | **Read Term** | **ICD-Code** |
| --- | --- | --- | --- |
| 3968 | B34..00 | Malignant neoplasm of female breast | C50 |
| 348 | B34..11 | Ca female breast |  |
| 26853 | B340.00 | Malignant neoplasm of nipple and areola of female breast | C50 |
| 23380 | B340000 | Malignant neoplasm of nipple of female breast | C50 |
| 64686 | B340100 | Malignant neoplasm of areola of female breast | C50 |
| 59831 | B340z00 | Malignant neoplasm of nipple or areola of female breast NOS | C50 |
| 31546 | B341.00 | Malignant neoplasm of central part of female breast | C50 |
| 29826 | B342.00 | Malignant neoplasm of upper-inner quadrant of female breast | C50 |
| 45222 | B343.00 | Malignant neoplasm of lower-inner quadrant of female breast | C50 |
| 23399 | B344.00 | Malignant neoplasm of upper-outer quadrant of female breast | C50 |
| 42070 | B345.00 | Malignant neoplasm of lower-outer quadrant of female breast | C50 |
| 20685 | B346.00 | Malignant neoplasm of axillary tail of female breast | C50 |
| 49148 | B347.00 | Malignant neoplasm of overlapping lesion of breast | C50 |
| 56715 | B34y.00 | Malignant neoplasm of other site of female breast | C50 |
| 95057 | B34y000 | Malignant neoplasm of ectopic site of female breast | C50 |
| 38475 | B34yz00 | Malignant neoplasm of other site of female breast NOS | C50 |
| 9470 | B34z.00 | Malignant neoplasm of female breast NOS | C50 |
| 7833 | B830.00 | Carcinoma in situ of breast | D05 |
| 10387 | B830000 | Lobular carcinoma in situ of breast | D05 |
| 18694 | B830100 | Intraductal carcinoma in situ of breast | D05 |
| 18029 | BB9..00 | [M]Ductal, lobular and medullary neoplasms |  |
| 27728 | BB90.00 | [M]Intraductal carcinoma, noninfiltrating NOS |  |
| 8351 | BB91.00 | [M]Infiltrating duct carcinoma |  |
| 21833 | BB91.11 | [M]Duct carcinoma NOS |  |
| 30189 | BB91000 | [M]Intraductal papillary adenocarcinoma with invasion |  |
| 39760 | BB91100 | [M]Infiltrating duct and lobular carcinoma |  |
| 62871 | BB92.00 | [M]Comedocarcinoma, noninfiltrating |  |
| 58131 | BB93.00 | [M]Comedocarcinoma NOS |  |
| 40359 | BB94.00 | [M]Juvenile breast carcinoma |  |
| 67701 | BB94.11 | [M]Secretory breast carcinoma |  |
| 16677 | BB9B.00 | [M]Medullary carcinoma NOS |  |
| 47920 | BB9B.11 | [M]C cell carcinoma |  |
| 50946 | BB9C.00 | [M]Medullary carcinoma with amyloid stroma |  |
| 98883 | BB9D.00 | [M]Medullary carcinoma with lymphoid stroma |  |
| 21861 | BB9E.00 | [M]Lobular carcinoma in situ |  |
| 9956 | BB9E000 | [M]Intraductal carcinoma and lobular carcinoma in situ |  |
| 12427 | BB9F.00 | [M]Lobular carcinoma NOS |  |
| 7319 | BB9G.00 | [M]Infiltrating ductular carcinoma |  |
| 32472 | BB9H.00 | [M]Inflammatory carcinoma |  |
| 12300 | BB9J.00 | [M]Paget’s disease, mammary |  |
| 60803 | BB9J.11 | [M]Paget’s disease, breast |  |
| 42542 | BB9K.00 | [M]Paget’s disease and infiltrating breast duct carcinoma |  |
| 12480 | BB9K000 | [M]Paget’s disease and intraductal carcinoma of breast |  |
| 3969 | BB9M.00 | [M]Intracystic carcinoma NOS |  |
| 60683 | BB9z.00 | [M]Ductal, lobular or medullary neoplasm NOS |  |
| 12499 | Byu6.00 | [X]Malignant neoplasm of breast |  |
| 53803 | ByuFG00 | [X]Other carcinoma in situ of breast | D05 |
| 16639 | ZV10300 | [V]Personal history of malignant neoplasm of breast |  |

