Exposure: patients will be considered exposed to exogenous hormones if they have at least one prescription for a hormonal contraceptive or hormone replacement therapy preparation (as defined in the British National Formulary (BNF)) within the observation period (start of follow-up to index date). Sensitivity analyses will be performed restricting the definition of exposure to those with 2 or more prescriptions. OC/HT type will be assigned based on BNF classification, classing women with separate prescriptions on the same day for oestrogen and progestagen as being prescribed combined oestrogen-progestagen therapy.

Outcomes: incident invasive and *in situ* cancers of the breast (ICD-10 C50 and D05)

Covariates: smoking status, alcohol drinking [most recent record before index date], body mass index [most recent record at least 2 years before index date, to account for reverse causality] and parity will be taken into account where possible in adjusted and/or stratified analyses. Availability of prescription data will allow medications such as aspirin and bisphosphonates, which may be related to breast cancer risk and to hormone use, to be considered in supplementary analyses.

Data/statistical analysis outline methodology

Conditional logistic regression will be used to estimate crude and adjusted odds ratios (relative risks) with 95% confidence intervals for cancer risk in relation to hormone prescription vs no prescription within the observation period. Analyses for hormonal contraceptives will include hormone type and mode of delivery, including progestagen-only contraception; for HT, hormone type, mode of delivery and timing of use; for both, the risks associated with use of Mirena will be examined. Adjustment variables will include smoking status (never, current, past, unknown), alcohol drinking (none, some, unknown) and body mass index (<25, 25-30, 30+ kg/m sq, unknown) and where possible, parity (at least nulliparous, parous, unknown). Data analysis will be carried out using STATA software v10. Analyses for HT will generally be restricted to women aged over 40, and for OC use to women aged 20-50 years.

Patient/user group involvement

None

Limitations of study design, data sources, analytic methods

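### The code list that flags incident breast cancer contains a personal-history code, so women with past disease can be counted as incident cases

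*Protocol*

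**What the plan says.** The amendment's case definition (Protocol, Revised definitions of cases and controls) gives Appendix 1 one stated purpose: "The list of Read codes used to flag women with incident breast cancer diagnosis as per previous protocol is shown Appendix 1". The same paragraph adds: "Women are excluded if they have a past history of invasive or in situ breast cancer". The original exclusion criteria under Study population say the same.

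The final row of Appendix 1 is ZV10300, "V]Personal history of malignant neoplasm of breast". The list also holds 25 BB9 morphology codes, among them "M]C cell carcinoma" (BB9B.11) and "M]Medullary carcinoma with amyloid stroma" (BB9C.00). The outcome under Exposures, outcomes, covariates is incident invasive and in situ breast cancer, coded "ICD-10 C50 and D05".

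Two other rules matter. All women need at least 12 months of up-to-standard data before the index date, which for a case is the date of diagnosis. Exposure is at least one prescription between the start of follow-up and the index date.

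**The concern.** A code that means the disease lies in the past sits on a list whose stated job is to identify new disease. The protocol shows no other list, gives ZV10300 no separate role, and has no rule for a woman whose first listed code is the history code.

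What is at stake is time order. A nested case-control analysis needs exposure to be measured before the outcome. For a woman flagged by ZV10300, the index date is the day her history was recorded, so some or all of the window in which her prescriptions are counted comes after her cancer. If hormone prescribing is lower after breast cancer, which is an assumption here, she looks like an unexposed case and the odds ratio is pulled down. Adjusting for smoking, alcohol, body mass index and parity cannot repair that, and a larger sample does not reduce it.

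**Working it through.** **Reading the rules together.**
1. Suppose a woman had breast cancer before joining the practice and her record holds no listed code until ZV10300 is entered in, say, year 3.
2. She has more than 12 months of data before that date, so she passes the look-back. Had the code been entered in the first 12 months, she would have failed it.
3. Her first listed code is on the list that flags incident cases, so she can be flagged with an index date in year 3.
4. The past-history exclusion stops this only if ZV10300 itself is used as evidence of past disease. The protocol does not say that it is.

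**Counting Appendix 1.** There are 48 codes: 16 mapped to C50, 4 to D05 and 28 with a blank ICD cell (16 + 4 + 28 = 48). The 28 blanks are 25 BB9 codes, B34..11, Byu6.00 and ZV10300. Of the 25 BB9 terms, 6 name breast or mammary and 19 do not.

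**Illustrating the size.** The protocol states no figure for this point that could be reproduced. One input comes from it: HT prevalence of about 33% in women over 40 (Sample size and power calculations), used as control exposure p0. Two inputs are assumptions: the share x of flagged cases that are really past disease, and their exposure q.

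- Control odds: 0.33/0.67 = 0.4925.
- Exposure in true cases: p1 = 0.4925 × OR / (1 + 0.4925 × OR). This is 0.3514 for OR 1.10 and 0.4962 for OR 2.0.
- Exposure in flagged cases: pc = (1 − x) × p1 + x × q.
- Observed OR = [pc/(1 − pc)] / 0.4925.

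With x = 3%, q = 5% and OR 1.10: pc = 0.97 × 0.3514 + 0.03 × 0.05 = 0.3424, odds 0.5206, observed OR 1.06. With OR 2.0: pc = 0.97 × 0.4962 + 0.0015 = 0.4829, odds 0.9337, observed OR 1.90. With x = 1% and OR 2.0: pc = 0.4918, odds 0.9676, observed OR 1.96.

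| True OR | Assumed q | x = 1% | x = 3% | x = 5% |
|---|---|---|---|---|
| 1.10 | 5% | 1.09 | 1.06 | 1.03 |
| 1.10 | 16.5% (half of controls) | 1.09 | 1.07 | 1.06 |
| 1.10 | 33% (same as controls) | 1.10 | 1.10 | 1.09 |
| 2.0 | 5% | 1.96 | 1.90 | 1.83 |
| 2.0 | 16.5% | 1.97 | 1.92 | 1.87 |
| 2.0 | 33% | 1.99 | 1.96 | 1.93 |

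For scale, the amendment says that the first extract held 33,000 cases, so 1% is 330 women and 3% is 990.

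**Why small effects matter.** The protocol claims power for a relative risk below 1.1. An unmatched calculation with its 10,000 cases gives a detectable OR at 33% prevalence of 1.07 with 40,000 controls and 1.08 with 20,000, so the claim reproduces. A shift from 1.10 to 1.06 is of the same order as the effects that the study says it can detect.

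**The case against.** The best defence is that the exclusion already covers these women. The protocol excludes past history without asking for an earlier dated record, and ZV10300 is itself a statement of past history. Appendix 1 is headed as a list for breast cancer diagnosis, without the word incident. It is the only list shown, and controls must also be free of any breast cancer diagnosis, for which ZV10300 is suitable. This stands in part: the text permits misclassification but does not show that it occurs. It does not remove the point, because the only use that the amendment assigns to the list is flagging incident cases.

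A reader might also infer that all 19 BB9 terms without a breast word bring in non-breast tumours. The documents do not support that. Most are ductal, lobular or comedo histologies, and the appendix itself uses lobular and intraductal carcinoma for in situ disease of the breast. Nor does a blank ICD cell show anything: the code for cancer of the female breast (B34..11) is blank too. What remains is a few non-specific terms, for example "M]C cell carcinoma", "M]Medullary carcinoma with amyloid stroma" and the group term for ductal, lobular and medullary neoplasms (BB9..00). Nothing in those words ties them to C50 or D05. Tumours unrelated to hormones would dilute an odds ratio towards 1, not below it.

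The size is also open to challenge. Neither the share nor the 5% exposure is in the documents, and 5% is an unfavourable choice, because part of the window may precede the true diagnosis. With exposure as in controls, the effect is small. That is fair, and it is why the table shows a range.

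**Conclusion.** The point holds for ZV10300: a code for past disease is on the list that flags incident disease, against the protocol's own exclusion, and no rule resolves the conflict. The supportable conclusion is that women with past breast cancer can enter as incident cases, with exposure measured partly or wholly after the outcome. It would go too far to say that they do enter, or in what number.

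Over the assumed range of 1% to 5% of cases and 5% to 33% exposure, a true OR of 2.0 is observed as 1.99 to 1.83 and a true OR of 1.10 as 1.10 to 1.03. Large HT effects would survive, while effects near 1.1 could lose much of their size. These figures are illustrations that rest on the assumed share and exposure, and the share can be counted in the extract. The morphology point is secondary and limited to the few non-specific terms. No sample-size figure changes.

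**What to change.** At the full dataset refresh that the amendment already requests:

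1. Remove ZV10300 from the case-flag list and use it only to exclude women with past disease. For cases, it excludes when dated before the first diagnosis code; a history code entered after a qualifying diagnosis should not remove a true case. For controls, it excludes at any date up to the last extraction. A woman with ZV10300 alone is then neither case nor control.
2. Accept the few non-specific morphology codes only alongside a breast-site code (B34, B830, Byu6 or ByuFG), or drop them.
3. Add a sensitivity analysis restricted to cases with a breast-site code. Requiring a site code for every BB9 term in the main analysis is not advised, because it could discard true cases recorded only by histology.
4. Report how many women have ZV10300 as their first listed code.

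The cost is an edit to Appendix 1, probably slightly fewer cases, and dropping or rebuilding the affected matched sets, since each control takes its case's index date. Done at the refresh, the added work is small.
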